#### Participant timeline

Patients are identified in the AMU and ED by research staff according to eligibility criteria and once written informed consent is obtained they are immediately randomised to the intervention or control group. Those randomised to the intervention group have a nose and throat swab performed immediately by a study doctor or research nurse and this is then tested on the FilmArray machine. Results are available after approximately 1 h and are immediately communicated to the clinical team. Clinical data is then collected retrospectively for both groups. There are no follow up visits for either group.

#### Sample size

Sample size is based upon the primary outcome measure of proportion of patients treated with antibiotics. Previous studies have demonstrated that around 75% of patients hospitalised in the UK with acute respiratory illness are treated with antibiotics [2]. Two small studies in hospitalised adult patients with acute respiratory illness have demonstrated reductions in the proportion of patients treated with antibiotics of around 10–15% in those tested for respiratory viruses [44, 52]. To detect a reduction in antibiotic use from 75 to 65% with a power of 0.8 and significance level of 0.05, 326 patients would be required in each group. Allowing for withdrawals in up to 10% of patients we aim to recruit 360 patients to each group (720 patients in total).

#### Recruitment and screening

Eligible patients in the emergency department (ED) and acute medicine unit (AMU) of Southampton General Hospital will be identified by research staff who will regularly review the comprehensive IT admissions systems in each area on a daily basis. Recruitment will run from January 2015 until April 2015 and from October 2015 to April 2016 in order to include the periods of peak influenza circulation for those seasons.

### Assignment of interventions

#### Sequence generation, allocation concealment and implementation

Once an eligible patient has been screened, and given fully informed, written consent they will be enrolled and assigned a unique participant identification number consecutively. A study team member will then use a dedicated internet-based randomisation service (sealedenvelope.com, which uses random permuted blocks of varying sizes) to obtain a computer generated randomisation code for the patient which will assign them to either the intervention or control group. Research staff will implement the allocation sequence and assign the patients to the group based on the allocation code from sealedenvelope.com.

#### Blinding

As this is a pragmatic trial of a diagnostic device no attempt at blinding trial participants, research staff or care providers will be made. Data analysts will be blinded to group allocation.

### Data collection, management and analysis

#### Data collection methods

Clinical and demographic data will be collected at the time of enrolment by research staff from patient paper case notes and electronic medical records. Outcome data will be collected retrospectively by research staff from paper case notes, electronic medical records, electronic prescribing systems, and electronic radiological and laboratory results systems. Final clinical diagnosis will be based on clinical discharge coding and discharge summaries. All source data will be entered into a standardised paper case report form. Patients withdrawn from the study will have no further data collected. Missing data was minimal in the pilot study and is not expected to be a significant issue; the use of multiple imputation will be considered should missing data exceed 10% in the primary outcome.

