**Methods:**

The ResPOC study is a pragmatic randomised controlled trial of molecular point-of-care testing for respiratory viruses in adults with acute respiratory illness presenting to a large teaching hospital in the United Kingdom. Eligible participants are adults presenting with acute respiratory illness to the emergency department or the acute medicine unit. Participants are allocated 1:1 by internet-based randomisation service to either the intervention of a nose and throat swab analysed immediately on the FilmArray Respiratory Panel as a POCT or receive routine clinical care. The primary outcome is the proportion of patients treated with antibiotics. Secondary outcomes include turnaround time, virus detection, neuraminidase inhibitor use, length of hospital stay and side room use. Analysis of the primary outcome will be by intention-to-treat and all enrolled participants will be included in safety analysis.

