### Trial design

This is a pragmatic randomised controlled trial with parallel groups allocated 1:1 to the intervention (POCT) and control (routine clinical care) arms. The framework is superiority. The study protocol adheres to the SPIRIT statement [50].

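### Ending all data collection at withdrawal, whatever the kind of withdrawal, loses safety and primary-outcome data that routine records could still supply

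*Protocol article*

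**What the plan says.** The relevant statements in the protocol article are these.

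- **Data collection methods:** "Patients withdrawn from the study will have no further data collected". No kinds of withdrawal are distinguished. The same section says that missing data were minimal in the pilot, and that multiple imputation will be considered if more than 10% of primary outcomes are missing.
- **Abstract, Methods:** "Analysis of the primary outcome will be by intention-to-treat and all enrolled participants will be included in safety analysis". The Statistical methods section repeats intention-to-treat for the primary outcome, with a chi-square test.
- **Harms:** the serious adverse events include death in hospital or up to 30 days after enrolment, and intensive care admission.
- **Sample size:** "Allowing for withdrawals in up to 10% of patients we aim to recruit 360 patients to each group (720 patients in total"), starting from 326 per group.
- **Primary outcome and Participant timeline:** antibiotic treatment is read from case notes after the event, over the hospital stay or 30 days if that is shorter. "There are no follow up visits for either group".

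**The concern.** In many trials, withdrawal makes outcome data unobtainable because the patient no longer attends. That is not so here. Apart from optional stored samples in a subgroup, the only trial procedure is one swab in the intervention arm. The outcomes lie in case notes, prescribing systems and other hospital records whether or not the patient continues with study procedures. A patient who refuses further sampling but does not object to use of the records could be followed to 30 days with no contact. The rule as worded stops this.

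Two commitments are affected. The safety analysis is to cover everyone enrolled, yet events after withdrawal could not be recorded. The primary analysis is to be by intention-to-treat, yet it would rest on those not withdrawn. A statistical analysis plan can say how missing values are handled, but it cannot recover data that the protocol tells staff not to collect.

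**Working it through.** **1. Does the plan treat withdrawn patients as lost?**

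Inputs from the Sample size section: 75% v 65%, power 0.80, significance level 0.05 (sidedness is not stated; two-sided assumed).

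With unpooled variance, n per group = (1.960 + 0.842)² × (0.75×0.25 + 0.65×0.35) / 0.10² = 7.849 × 0.415 / 0.01 = 325.7, so 326. The stated figure reproduces.

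Allowing for 10% withdrawal, 326 / 0.90 = 362.2 (363), and 326 × 1.10 = 358.6 (359). The stated 360 lies between the two. The inflation only makes sense if withdrawn patients have no primary outcome, which agrees with the data collection rule.

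**2. How many are lost at the ceiling?**

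360 × 0.10 = 36 per arm, or 72 of 720, leaving 324 per arm. This is an upper limit, because a positive outcome may already have been recorded for some patients before they withdrew. A rate of exactly 10% does not exceed 10%, so the imputation clause is not reached.

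**3. Power**

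Power = Φ[(0.10√n − 1.960 √(2×0.70×0.30)) / √0.415]

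- n = 324: (1.800 − 1.270) / 0.644 = 0.822, giving 79.5%.
- n = 360: (1.897 − 1.270) / 0.644 = 0.974, giving 83.5%.

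Losing the full allowance costs about 4 points of power and leaves it close to the planned 80%.

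**4. Extreme bounds on the primary difference**

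Suppose that the observed patients show 75% v 65%. The lower bound has every missing intervention patient treated and no missing control treated. The upper bound has the reverse.

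| Withdrawn per arm | Observed per arm | Lower bound | Upper bound |
|---|---|---|---|
| 10% (36) | 324 | (243 − 246.6)/360 = −1.0 points | (279 − 210.6)/360 = +19.0 points |
| 5% (18), assumed | 342 | (256.5 − 240.3)/360 = +4.5 | (274.5 − 222.3)/360 = +14.5 |
| 2% (7), assumed | 353 | (264.75 − 236.45)/360 = +7.86 | (271.75 − 229.45)/360 = +11.75 |

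At the ceiling the half-width is 10 points, equal to the target effect.

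**5. A milder illustration (all rates assumed)**

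True use is 75% in both arms, a share w withdraws, and a share r of those withdrawn received antibiotics. The observed rate is (0.75 − w·r)/(1 − w).

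- r = 0.50: w = 0.10 gives 0.700/0.90 = 77.8%; w = 0.02 gives 0.740/0.98 = 75.5%. The spurious gap is 2.3 points.
- r = 1.00: w = 0.10 gives 0.650/0.90 = 72.2%; w = 0.02 gives 0.730/0.98 = 74.5%. The gap is 2.3 points in the other direction.

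Within this range of r, 2.3 points is the maximum. Use below 50% among the withdrawn would give more.

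**6. Safety**

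No arithmetic is needed. The abstract includes all enrolled participants, Harms counts deaths to 30 days, and the data collection rule stops at withdrawal. A patient who withdraws on day 2 and dies on day 20 is in the promised population, with an event that the rule forbids recording.

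**The case against.** The strongest reply is that the rule concerns patients withdrawn from the study, and nothing says that refusing a procedure counts as withdrawal. In the control arm, taking part is almost wholly a matter of record access, so withdrawal there would largely mean withdrawing permission, and stopping is then proper. A fuller definition may stand in the full protocol or consent form, neither of which is shown. This has weight, but the sentence in the article is an instruction without qualification. Followed as written, it stops collection in both cases.

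Several stronger readings are tempting, and the document does not support them.

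- **A flat contradiction of intention-to-treat.** Patients can be analysed as randomised with some outcomes missing. That is a missing-data problem, and the plan is open about its allowance. The conflict is direct only for safety, and even there one could count each patient up to withdrawal; deaths after that would still be missed.
- **Expected arm-dependent withdrawal.** A reader might infer it from the open-label design, through swab refusal or disappointment at being a control. Patients who decline swabbing are excluded, and the swab follows randomisation at once. Nothing in the article speaks to disappointment among controls.
- **Deletion of data already held.** The rule stops further collection and does not order deletion. The protection is partial, because outcomes are abstracted retrospectively and absence of antibiotic use cannot be settled before the window closes.
- **A fault in leaving missing data at or below 10% without a set method.** Sensitivity analyses commonly belong to the statistical analysis plan, which is not shown.

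**Conclusion.** The point stands as a correctable flaw in a stated rule. Followed literally, the rule leaves deaths and intensive care admissions after withdrawal uncounted, despite the commitment to all enrolled participants, and makes the primary analysis a complete-case analysis of those not withdrawn. Much of that loss is unnecessary, because the data lie in routine records.

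The likely size is small. The 10% is a planning ceiling and not a forecast, the pilot had minimal missing data, and one swab with no visits gives little reason to withdraw. A reader might take the plus or minus 10 points as the expected bias. It is an extreme bound that needs every missing patient treated in one arm and none in the other. The 2.3-point figure rests on an assumed 10% v 2% imbalance and on assumed antibiotic use of 50% to 100% among the withdrawn; the article gives no withdrawal rates by arm. Power is not the issue. The change is worth making because it is cheap and removes an avoidable source of bias and of missed safety events.

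**What to change.** Amend the sentence in Data collection methods to distinguish two cases:

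1. **The patient stops a study procedure but does not withdraw permission to use records.** Continue to take the primary outcome and the 30-day safety data from routine records, and analyse the patient as randomised.
2. **The patient withdraws permission to use records.** Collect nothing after that date and keep the data up to it.

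State that the all-enrolled safety analysis includes patients in the second case up to their withdrawal date, so that this sentence, the abstract and Harms agree. Report withdrawals by arm and by type.

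The cost is a change to the protocol and consent wording, and one more item on the case report form to record the type of withdrawal. No visits or procedures are added.

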#### Data management

The study will be conducted in accordance with the approved protocol, ICH GCP relevant regulations and standard operating procedures. Data will be evaluated for compliance with the protocol and accuracy in relation to source documents. Data from case report forms will be entered into a secure bespoke database at the completion of the study followed by data lock. All data will be anonymised: volunteer participant data will be identified by a unique study number in the CRF and database. A separate confidential file containing identifiable information will be stored in a secured location in accordance with the Data Protection Act 1998. Only the Sponsor’s representative and investigators will have access to the information.

#### Statistical methods

This will be performed by a dedicated medical statistician from the University of Southampton independent from the study team. Patients tested with the rapid diagnostic test will be compared with patients treated by routine clinical care using standard descriptive and comparative statistical methods using Prism (GraphPad Software Inc; La Jolla, California) and SPSS (SPSS, Inc; Chicago, Illinois). Summaries of all baseline characteristics will be presented using means and standard deviations, medians and interquartile ranges, or frequencies and percentages, as appropriate. Analysis of the primary outcome will be by intention-to-treat and will compare the proportion of patients receiving antibiotics using the chi-square test for equality of proportions between groups. The effect of group (intervention or control) on the primary outcome will be further assessed using logistic regression to control for demographics (age, sex) and other co-variables. For secondary outcomes the intervention and control groups will be compared using chi-square tests for equality of proportions for binary data (including proportions) and using t-tests and non-parametric equivalent tests for continuous data (e.g. turnaround time) as appropriate.

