##### Secondary outcomes

Median duration of antibiotic use, daysProportion of patients receiving only a stat dose of antibioticsProportion of patients receiving <48 h antibioticsProportion of patients receiving intravenous antibioticsMedian duration of intravenous antibiotics, daysProportion of patients with influenza treated with influenza antiviralsProportion of influenza antiviral use occurring in patients with influenzaMedian time to influenza antiviral use, hoursMedian duration of influenza antivirals, daysMedian duration of hospital stay, daysProportion of patients admitted to a side room*Median duration of side room use, days*Median time to isolation or de-isolation, days*Median length of hospital stay, daysMedian turnaround time of respiratory viruses testing, hoursProportion of patients with viruses detectedProportionate mortality in hospital and at 30 days post randomisationProportion admitted to Intensive care or high dependency unitsProportion re-presenting to hospital within 30 daysProportion re-admitted to hospital within 30 daysProportion with prolonged in-patient stay

* A side room is a single-patient room; the use of which is a surrogate measure for isolation for the purpose of infection prevention and control.

Every attempt will be made to recruit patients and deliver the results of POCT prior to antibiotic use however it is understood due to the usual processes of care in hospital that on some occasions antibiotics will be have been administered before POCT is performed or before results are available to clinical teams. Therefore we plan to also undertake a *post hoc* analysis of only those patients where antibiotics were not administered prior to POCT results being available to clinicians.

In view of the deliberately broad inclusion criteria, heterogeneity of treatment effect among different clinical groups is anticipated and therefore subgroup analysis for the primary and certain key secondary outcome measures is planned based on clinical group. Results for antibiotic use (including any use, single dose, and use of less than 48 h duration), duration of antibiotics, admission and length of hospitalisation will be assessed separately for each clinical subgroup.

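### The primary analysis is a valid but unadjusted chi-square test in a deliberately mixed population; a prespecified baseline-adjusted risk difference would be more precise at little cost, and the supporting model should exclude post-randomisation diagnoses

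*Protocol article*

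**What the plan says.** The Statistical methods section of the protocol article gives an order of analysis for the primary outcome. By intention-to-treat, the proportions receiving antibiotics are compared "using the chi-square test for equality of proportions between groups". The effect of group is then "further assessed using logistic regression to control for demographics (age, sex) and other co-variables". Age and sex are the only covariates named.

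Four other parts of the article bear on this:

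- **Eligibility criteria.** Patients may have pneumonia, bronchitis, influenza-like illness, or an exacerbation of COPD, asthma or bronchiectasis. An AMU or ED clinician makes the provisional diagnosis.
- **Secondary outcomes.** "In view of the deliberately broad inclusion criteria, heterogeneity of treatment effect among different clinical groups is anticipated", and subgroup analyses by clinical group are planned, including for the primary outcome. Clinical group is not named as an adjustment covariate.
- **Sequence generation.** Allocation is by an internet service "which uses random permuted blocks of varying sizes". No stratification factor is named.
- **Data collection methods.** Clinical and demographic data are collected at enrolment. The final diagnosis is taken later, from discharge coding and discharge summaries.

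**The concern.** In a population this mixed, the reason for presentation may well predict whether a patient is given antibiotics. If it does, part of the outcome variance is explained by something known before randomisation. An unadjusted test leaves that variance in the error term, and nothing in the described allocation balances clinical group between the arms. The estimate remains unbiased and the test keeps its error rate, but the confidence interval is wider than it needs to be.

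The second issue is what the open covariate clause lets in. Two versions of the diagnosis exist: a provisional one at entry and a final one at discharge. The intervention is a diagnostic test whose result is reported to the clinical team, so it could change the discharge diagnosis. Adjusting for a variable that the intervention can alter may distort the estimated effect. The current wording does not exclude it.

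**Working it through.** **Inputs from the Sample size section.** Control proportion 0.75 ("around 75% of patients hospitalised in the UK with acute respiratory illness are treated with antibiotics"), intervention proportion 0.65, "with a power of 0.8 and significance level of 0.05, 326 patients would be required in each group". Allocation is 1:1 (Trial design). Sidedness is not stated; two-sided is used because it reproduces the plan's figure.

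**Step 1: reproduce the plan's figure.** With unpooled variance,

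n per arm = (1.960 + 0.842)² × (0.75 × 0.25 + 0.65 × 0.35) / 0.10²
= 7.849 × 0.415 / 0.01 = 325.7, which rounds up to 326.

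The pooled-variance version gives 329. The stated 326 therefore reproduces and agrees with an unadjusted comparison of proportions.

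**Step 2: unadjusted precision at 326 per arm.** Power with the pooled null variance is

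Φ[(0.10 − 1.960 × √(2 × 0.70 × 0.30 / 326)) / √(0.415 / 326)] = 79.7%.

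The 95% confidence half-width for the risk difference is 1.96 × √(0.415 / 326) = 0.070, or 7.0 percentage points.

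**Step 3: the assumption.** Let R² be the share of outcome variance explained by the baseline covariates. The documents give no value, so a range of 0.02 to 0.20 is assumed. As an approximation, adjustment multiplies the variance by (1 − R²). That is equivalent to 326 / (1 − R²) patients per arm analysed without adjustment, and the number needed for the planned power falls to 326 × (1 − R²).

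| Assumed R² | Equivalent n per arm | Power at 326 per arm | n per arm needed | Half-width (points) |
|---|---|---|---|---|
| 0 | 326 | 79.7% | 326 | 7.0 |
| 0.02 | 333 | 80.5% | 320 | 6.9 |
| 0.05 | 343 | 81.7% | 310 | 6.8 |
| 0.10 | 362 | 83.7% | 294 | 6.6 |
| 0.15 | 384 | 85.7% | 278 | 6.4 |
| 0.20 | 408 | 87.7% | 261 | 6.3 |

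**Step 4: what a mid-range R² would look like.** Take four equal-sized presenting groups with antibiotic rates of 95%, 82%, 62% and 61%. These rates are invented for illustration; their mean is 75%. The between-group variance is (0.20² + 0.07² + 0.13² + 0.14²) / 4 = 0.0204. Dividing by 0.75 × 0.25 = 0.1875 gives R² = 0.109. The equivalent sample is 326 / 0.891 = 366 per arm, and power is about 84%. An R² near 0.10 therefore requires large differences between presenting groups.

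**Step 5: timing of the two diagnoses.** Under Eligibility criteria the provisional diagnosis is part of entry. Under Participant timeline, randomisation follows consent, and the test result reaches the clinical team about an hour after testing. Under Data collection methods the final diagnosis comes from discharge records. Only the provisional diagnosis precedes randomisation and so is safe as a covariate.

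**The case against.** The case for leaving the plan alone is substantial, and most of it stands.

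- The chi-square test is valid under 1:1 randomisation, matches the sample-size method and already works on the proportion scale. Chance imbalance in case mix is ordinary sampling variation, which the test's error rate covers. This stands: nothing here is a validity error.
- A reader might infer that two competing primary analyses are planned with nothing to say which decides. The text does not support this. The chi-square comparison is the analysis of the primary outcome, and the logistic model further assesses it. The analysts are also to be blinded to allocation (Blinding), and the statistician is independent of the study team.
- A reader might also infer that the trial will report an odds ratio that exaggerates the effect. The article never says an odds ratio will be reported. At the design rates it would be (0.65/0.35) / (0.75/0.25) = 0.62, against a risk ratio of 0.65/0.75 = 0.87. But an odds ratio is correct on its own scale and misleads only if read as a risk ratio.
- A full covariate list for a supporting model is normally SAP material, and the unnamed covariates may include clinical group. This stands too: the incomplete list alone would not be a finding.
- The prognostic strength is assumed. Anticipated heterogeneity of treatment effect does not show that clinical group predicts antibiotic use. That is correct, and it is why the gain is given as a range that starts at nothing.

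Two things survive. A more precise primary analysis is available from data the trial already plans to collect at enrolment, and the covariate clause as worded does not keep out a diagnosis fixed after randomisation.

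**Conclusion.** The point holds as an inexpensive improvement. The planned primary test is sound but forgoes precision in a population described as deliberately broad. For an assumed R² of 0.02 to 0.20, the gain is about 1 to 8 percentage points of power at 326 per arm, and the confidence half-width falls from 7.0 to between 6.9 and 6.3 points. If clinical group and the other covariates are not prognostic, there is no gain. These figures rest on the variance approximation and on an R² that the documents do not supply.

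The post-randomisation diagnosis is a risk in the wording. The article does not say that the discharge diagnosis will be a covariate; it only fails to exclude it. Nothing here supports calling the chi-square test wrong.

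**What to change.** In Statistical methods, or in the SAP before data lock:

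1. Make the primary estimate a covariate-adjusted risk difference with 95% confidence interval, standardised from a logistic model in the intention-to-treat population.
2. Fix the covariates as age, sex, provisional clinical group and recruitment season (the two periods given under Recruitment and screening). All are known before randomisation.
3. Keep the chi-square test as the unadjusted supporting result.
4. Delete the open-ended reference to further covariates, and state that the discharge-coded diagnosis may not be used for adjustment.

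The cost is a few lines of text and code, with no extra patients. The primary result becomes slightly less simple to present. Provisional clinical group must be recorded in fixed categories, complete at baseline; the article says that clinicians make this diagnosis but does not say that it is captured in that form.
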